### Randomization and blinding

Participants will be randomized into the study, stratified by site and by medication resistance (2 or fewer adequate trial failures versus more than 2 adequate trial failures; an adequate trial of antidepressant is defined as an antidepressant trial ranked with an ATHF (score ≥ 3)). Prior rTMS trials have demonstrated that the degree of treatment resistance is a key predictor of response, and therefore, it is essential to ensure that the groups are balanced concerning this variable [12, 38, 39].

Patients will be randomized using random permuted blocks of varying sizes, with study personnel blinded to the block sizes. An independent assistant external to the study will manage the randomization using a computer generator. The participants’ number and treatment code will be assigned after their details (i.e., initials and number of failed adequate antidepressant trials) have been obtained. A unique treatment code, designated to either active or sham stimulation, allows for the technicians to remain blinded. Once the code is entered into the machine, it indicates which side of the A/P coil to place over the stimulation site and will only deliver pulses when the designated coil is placed correctly.

A specially designed rTMS coil containing both an active and a sham inductor head and identical external appearance will be used to ensure blinding during treatment. A computerized sensor instructs the technician to rotate the coil so that one side is in contact with the scalp. A pair of electrodes will also be placed close to the treatment spot, directly on the forehead, 1 cm apart from each other and secured with medical tape, in both active and sham groups. In the sham group, electrical pulses will be delivered through the scalp electrodes on each TMS pulse to further mimic the scalp sensations and muscle contractions associated with *verum* TMS. This approach is most likely to achieve both patient and technician blinding and is seen as the best possible sham for blinded rTMS treatment trials [24, 40].

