### Statistical methods

#### Clinical outcomes analysis

Primary Outcome Analysis: The primary outcome analysis on the change in HRSD-17 between baseline and end of treatment, will be conducted on an intention-to-treat basis. We plan to use multiple imputation methods developed by Schafer [62] to account for potential bias that may be incurred by missing data. Before the main effects analysis, descriptive statistics will be generated to summarize the data on all randomized participants to confirm that there are no group differences between the two conditions concerning baseline demographics and clinical characteristics. To assess for significant differences in treatment effects over time, a mixed-effects model with predictor variables for group (active vs. sham), time (baseline vs. end of treatment), and group-by-time interaction will be fitted to the data from the primary outcome measure (HRSD-17). The mixed-effects model will also be used to estimate the treatment effect over the full course of treatment.

Secondary Outcome Analyses: We will repeat the primary and secondary analyses in the same manner for the one-week post-treatment and four-week post-treatment time points. The same approach will be employed to assess treatment effects on the HRSD-6, SSI, BDI-II and GAD-7. Response and remission will be included as secondary clinical outcomes. Response will be defined as ≥ 50% reduction in symptoms on the primary outcome measure (HRSD-17) and remission will be defined as a post-treatment HRSD-17 < 8 [1]. We will use a conservative imputation that assumes non-remission or non-response if data is missing at the post-treatment assessment. A two-tailed Chi-squared test will assess the significance of any observed differences in the proportion of responders and remitters between groups based on pre- to post-treatment HRSD-17. Finally, we will summarize and compare the rates of adverse events, severe adverse events and dropouts in both groups.

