Exploratory Outcome Analyses: A multivariable regression model will be used to explore whether or not treatment resistance, patient expectancy, patient experience, or HCS modify the baseline adjusted treatment effect on the HRSD-17 (at day 5). The same analytic approach used for the primary outcome will be employed to assess for treatment effects on the HRSD-6, BDI-II, SSI and GAD-7. We will descriptively report the change from baseline to 5 days, 1-week, and 4-week post-treatment in the open-label 1 Hz right DLPFC phase and compare change, response, and remission in those who received active compared to sham stimulation in the blinded phase. Additionally, we will build a multiple regression model to explore how prior treatment condition, expectancy, and HCS score impact the baseline adjusted treatment effect in the open-label 1 Hz right DLPFC treatment group.

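### Site and medication resistance stratify the randomisation but enter neither the primary model nor the response and remission test, so standard errors are somewhat too wide and the tests conservative

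*Protocol article*

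**What the plan says.** Protocol article, Randomization and blinding: participants are "stratified by site and by medication resistance (2 or fewer adequate trial failures versus more than 2 adequate trial failures" (the parenthesis goes on to define an adequate trial). The reason given is that in earlier rTMS trials "the degree of treatment resistance is a key predictor of response", so the groups should be balanced on it. On the method of allocation: "Patients will be randomized using random permuted blocks of varying sizes".

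Protocol article, Clinical outcomes analysis: the primary mixed model is described by its terms, "group (active vs. sham), time (baseline vs. end of treatment), and group-by-time interaction will be fitted to the data from the primary outcome measure". The same approach is carried to the one-week and four-week time points and to HRSD-6, SSI, BDI-II and GAD-7. For the binary outcomes: "A two-tailed Chi-squared test will assess the significance of any observed differences in the proportion of responders and remitters between groups".

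Site appears in no described analysis. Resistance appears once, in an exploratory regression meant to "explore whether or not treatment resistance, patient expectancy, patient experience, or HCS modify the baseline adjusted treatment effect".

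**The concern.** Stratified blocks balance site and resistance across the arms, so differences between strata contribute almost nothing to the true sampling error of the treatment effect. An analysis that ignores the strata still counts those differences as residual noise. The reported standard error is then larger than the true one, confidence intervals are too wide, and the test rejects less often than its nominal level under the null. Some of the precision that the design could deliver is not used. The protocol itself calls resistance prognostic, so the effect should not be assumed to be exactly zero. The omission runs through every efficacy comparison of the blinded phase.

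**Working it through.** **Inputs.** From Sample size: difference 3 points, post-treatment SD 8, pre-post correlation 0.27, 80% power, 105 evaluable per group. Assumed: two-sided alpha 0.05 (not stated there, but it reproduces 105); R² between 2% and 20% (the documents give none); strata exactly balanced between arms.

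**Step 1. Reproduce 105.** Baseline-adjusted SD = 8 × sqrt(1 − 0.27²) = 7.703. Then n = 2 × (1.960 + 0.842)² × 7.703² / 3² = 103.5, so 104 per group. A t-based calculation gives 105 (power 80.2%). The planned size therefore rests on a baseline-adjusted variance. At 105 per group the standard error is 7.703 × sqrt(2/105) = 1.063, and 3/1.063 = 2.822. Normal-approximation power is Φ(2.822 − 1.960) = 80.6%.

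**Step 2. Effect of ignoring the strata.** Let R² be the share of the variance of the analysed contrast that the strata explain, and k = 1/sqrt(1 − R²).

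- Model SE / true SE = k
- Actual type I error = 2 × [1 − Φ(1.960k)]
- Unadjusted power = Φ((2.822 − 1.960)k)
- Adjusted power = Φ(2.822k − 1.960)

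For R² = 10%, k = 1.054: type I error = 2 × [1 − Φ(2.066)] = 3.9%; unadjusted power = Φ(0.909) = 81.8%; adjusted power = Φ(1.015) = 84.5%.

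| R² (assumed) | SE too wide by | Actual type I error | Power, unadjusted | Power, adjusted | n per group for 80% power, adjusted |
|---|---|---|---|---|---|
| 2% | 1.0% | 4.8% | 80.8% | 81.3% | 102 |
| 5% | 2.6% | 4.4% | 81.2% | 82.5% | 99 |
| 10% | 5.4% | 3.9% | 81.8% | 84.5% | 94 |
| 20% | 11.8% | 2.8% | 83.2% | 88.4% | 83 |

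At R² = 0 the last column would be 104.

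**Step 3. The scale.** The listed model, with two time points and a group-by-time term, estimates a difference in change. Its SD is sqrt(8² + b² − 2 × 0.27 × 8 × b), where b is the baseline SD, which the documents do not give. For b = 4 this is 7.92 and power at 105 per group is 78.4%; for b = 8 it is 9.67 and 61.4%. The table therefore describes the baseline-adjusted analysis behind the sample size, not the absolute power of the listed model. The mechanism is the same for change, but R² must then be the share of change-score variance: a stratum difference that is equal at baseline and day 5 cancels.

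Simulation check (3,000 runs, 104 per group in four equal strata, b = 4, resistance explaining 10% of baseline-adjusted variance). For the change contrast, type I error was 3.6% unadjusted and 4.5% adjusted, and power 78.3% and 81.4%. For ANCOVA, type I error was 3.4% and 4.3%, and power 80.7% and 83.5%. Monte Carlo error is about 0.4 points for type I error and 0.7 for power. At R² = 2% the power of the two analyses differed by less than one point.

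**Step 4. Which terms matter.** In one simulated data set the group-by-time standard error was 1.035 from the listed model, 1.035 after adding site and resistance as main effects, and 0.945 after adding site-by-time and resistance-by-time. A main effect that is constant over time drops out of the within-patient difference.

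**Step 5. Response and remission.** Simulation with 4,000 runs, 116 per group, two equal resistance strata, all rates assumed.

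| Sham rates by stratum | Active rates | Type I error, chi-squared vs Cochran-Mantel-Haenszel | Power, chi-squared vs Cochran-Mantel-Haenszel |
|---|---|---|---|
| 35% / 10% | 53% / 22% | 3.9% vs 5.0% | 72.3% vs 75.3% |
| 25% / 15% | 42% / 28% | 4.6% vs 4.8% | 72.5% vs 73.0% |

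With strongly prognostic strata the difference is visible; with weaker ones it is negligible.

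**The case against.** The document is a condensed article, and covariates are often left to the SAP, which is not shown. The model sentence does not call its list exhaustive and leaves out the random-effects structure. That is fair, and a SAP may add the factors. But the fixed terms are listed one by one and the binary test is named, so anyone who follows the text will omit the strata.

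The size is also open to challenge. No R² is documented, nothing is said about how prognostic site is, and below an R² of about 10% the power difference is under 3 points. The error is on the conservative side. This stands, and it limits the weight of the point. The exploratory regression does contain resistance, but it does not alter the primary test.

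A reader might infer that the omission leaves the trial underpowered against its plan, or wastes the stratification. The documents support neither. On the planning scale, unadjusted power stays at or slightly above 80% across the range. The power below 80% in Step 3 comes from using change instead of baseline adjustment, not from the strata. The stated purpose of stratifying is balance between groups, and that is kept whatever model is fitted.

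**Conclusion.** The mismatch between design and analysis is real. Its consequence is conservative inference: a standard error 1% to 12% too wide and an actual type I error of 4.8% down to 2.8%. The power forgone relative to an adjusted analysis is about half a point to 5 points. These figures hold for an assumed R² of 2% to 20% of baseline-adjusted variance, 105 per group, two-sided alpha 0.05 (assumed) and balanced strata. The treatment estimate is not biased, false positives are not inflated, and there is no shortfall against the planned 80% from this cause. For response and remission the loss may be negligible. The omission itself is certain from the text; its size is not. The change is worth making because it costs almost nothing.

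**What to change.** State that the primary analysis includes the randomisation factors, in one of two forms:

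- an ANCOVA of day-5 HRSD-17 on group, baseline HRSD-17, site and resistance stratum; or
- the mixed model with site-by-time and resistance-by-time terms added. Main effects alone would leave the group-by-time estimate unchanged.

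Use the same form for the other continuous scales and the later time points. For response and remission, use a Cochran-Mantel-Haenszel test stratified by site and resistance, or a logistic model containing both.

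Stratum sizes are not given, so add a rule for pooling strata if a cell is sparse. Fix all of this before unblinding, so that the covariates cannot be seen as chosen from the data. The cost is a few lines of wording: both factors are needed for allocation and so are already known, and no extra patients or visits are required.

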**Fig. 1 Fig1:**
[figure not shown]
Study flow chart

Following randomization, patients will undergo a series of assessments and motor threshold testing to determine the appropriate strength of stimulation. Depressive symptoms will be assessed using the Hamilton Depression Rating Scale (HRSD-17) [26]. The primary outcome analysis will include the change in HRSD scores from baseline to the end of the acute treatment. The HRSD-17 was selected to facilitate the comparison of outcomes in this trial to that of previous trials, since the HRSD has been standard in both rTMS and pharmacotherapy trials of patients with depression for decades [27–31]. The HRSD-6 [32], derived from the HRSD-17, will also be included as a secondary outcome measure. The Scale for Suicide Ideation (SSI) and self-report scales of depression and anxiety (Beck Depression Inventory, BDI-II and the General Anxiety Disorder, GAD-7), will also be completed. Side effects will be recorded at every visit and after every treatment session. Final assessments will be completed immediately after the last treatment. The one-week and four-week follow up assessments will be allowed within 1–2 days of the scheduled time points. Refer to Table 1 for a detailed schedule of assessments.

All treatments will be conducted with minimized personal contact (i.e., verbal communication) between the technician and patient to reduce the impact of nonspecific therapeutic contact on outcomes. The relevance of alliance extends beyond psychotherapy and has been shown to impact pharmacological interventions [33]. As a way to quantify the nonspecific active component of the treatment, a modified Human Connections Scale (HCS) will be administered following each treatment course (blinded and open label) to determine the impact of the patient’s sense of alliance with the technician on the therapeutic outcome [34]. This scale will be used as a secondary measure and explored with respect to its role in the treatment outcome.

Open Label: To ensure that all patients can receive a form of active treatment, those who have not achieved the response criterion (i.e., a 50% improvement from baseline on the HRSD-17) at the week four follow-up visit will be offered a second course of treatment, regardless of whether they initially received active or sham treatment.

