### Attendance and withdrawal criteria

Patients will be encouraged to attend all scheduled treatments. Those that meet the following criteria will be excluded from the per protocol analysis if they:

Miss / fail to attend any one of the five treatment days in the course overall.Miss / fail to attend more than five treatment sessions over the five days.Cannot tolerate stimulation of at least 90% RMT for the entire session on more than five treatment sessions.Develop active suicidal ideation with intent during the course of stimulation, or in the opinion of the site PI, that participation is not clinically indicated.Are admitted to hospital during the course of treatment.Withdraw consent to participate.

Patients will be discontinued if they experience worsening in depression, defined as an increase in HRSD-17 from a baseline of more than 25% at the post-treatment assessment or development of active suicidal intent or attempted suicide.

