### Sample size

We will consider the 8 × 5 protocol successful if the active stimulation group achieves superior improvement (i.e., a larger reduction in the mean HRSD-17 score) versus sham on the HRSD-17. To detect the minimally clinically significant difference of three points [61] on the HRSD-17 with 80% power (based on post-treatment HRSD-17 standard deviation of 8 and pre-post correlation of 0.27 in the iTBS group in the THREE-D trial [19]), 105 patients per group are needed. We expect a low attrition of 10% given that the treatment course is only five days, increasing the number required to be randomized to 116 per group (232 in total).

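### The Week-1 and Week-4 models leave out the Visit-5 HRSD-17 that the protocol uses to discontinue patients, so the follow-up effects can be biased toward the null

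*Protocol article*

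**What the plan says.** Clinical outcomes analysis specifies the primary mixed model with group, "time (baseline vs. end of treatment), and group-by-time interaction will be fitted to the data from the primary outcome measure (HRSD-17"). The analysis is by intention to treat, with multiple imputation for missing data. For the later visits the same section says "We will repeat the primary and secondary analyses in the same manner for the one-week post-treatment and four-week post-treatment time points", and it applies the same approach to HRSD-6, SSI, BDI-II and GAD-7.

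Table 1 schedules four HRSD-17 ratings in the blinded phase: baseline, Visit 5, Week 1 and Week 4.

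Attendance and withdrawal criteria states that patients will be discontinued for worsening, "defined as an increase in HRSD-17 from a baseline of more than 25% at the post-treatment assessment". Clinical assessments during and after treatment places that rating on the Friday of treatment, Visit 5. The section does not say whether discontinued patients are still rated at Weeks 1 and 4.

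**The concern.** Repeating a two-level model in the same manner gives three separate fits, each of baseline against one later visit. A fit holding only baseline and Week 4 is free of bias from missing data only if loss depends on nothing beyond baseline and arm. The discontinuation rule depends on the Visit-5 score. By the time it is applied, all 8 × 5 = 40 blinded sessions are over, so within the blinded phase little is left to discontinue except follow-up. If active treatment works, more sham than active patients cross the threshold. The sham patients lost are those with high scores, so the remaining sham group looks better than it should.

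At stake are the Week-1 and Week-4 contrasts, the trial's only randomised evidence on whether the five-day effect lasts. Non-responders "at the week four follow-up visit will be offered a second course of treatment", and that second course is open label.

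**Working it through.** **1. The plan's own figure.** Sample size gives a "minimally clinically significant difference of three points" "on the HRSD-17 with 80% power", with a "post-treatment HRSD-17 standard deviation of 8 and pre-post correlation of 0.27 in the iTBS group" of an earlier trial. Alpha is not stated; two-sided 0.05 is assumed.
- Baseline-adjusted SD = 8 × √(1 − 0.27²) = 7.70.
- n per arm = 2 × (1.96 + 0.84)² × 7.70² / 3² = 103.5, so 104. The noncentral t version gives 105, as stated.

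The inputs SD 8, r = 0.27 and 3 points are therefore used below.

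**2. How many the 25% rule touches.** Assumed, not in the documents: baseline mean 22 and SD 6; mean improvement 6 on sham and 9 on active, so Visit-5 means of 16 and 13. A patient meets the rule if Visit 5 − 1.25 × baseline > 0.
- SD of that quantity = √(8² + 1.25² × 6² − 2 × 1.25 × 0.27 × 6 × 8) = √(64 + 56.25 − 32.4) = 9.37.
- Active: mean 13 − 27.5 = −14.5; P = 1 − Φ(14.5/9.37) = 6%.
- Sham: mean 16 − 27.5 = −11.5; P = 1 − Φ(11.5/9.37) = 11%.
- With 5% random loss added: 1 − 0.95 × 0.94 = 11% of active and 1 − 0.95 × 0.89 = 15% of sham missing.

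**3. Effect on the Week-4 estimate.** This was simulated with 1,000,000 per arm, a true Week-4 effect of 3.0, and every patient who meets the rule unrated afterwards. Each arm's Week-4 mean is the observed mean plus b × (mean of the earlier scores in all patients − their mean in observed patients). The earlier scores are baseline only, or baseline with Visit 5.

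| Correlation Visit 5–Week 4 (assumed) | Baseline only | With Visit 5 |
|---|---|---|
| 0.5 | 2.72 | about 3.0 |
| 0.7 | 2.62 | about 3.0 |
| 0.85 | 2.52 | about 3.0 |

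The shortfall is 0.28 to 0.48 points, or 9% to 16% of 3.0. Repeat runs differed by at most 0.04.

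**4. Sensitivity.** A second set of assumptions used baseline mean 20 to 23 and SD 4.5, Visit-5 means 14 to 20 (active) and 17 to 23 (sham), and 10% random loss. The baseline-only estimate ran from 2.78 down to 2.06, and with Visit 5 from 2.98 to 3.03. The value 2.06 needs a sham arm with no average improvement and 24% of active and 32% of sham patients missing.

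**5. Precision.** At 116 per arm, under the 25% rule plus 5% random loss (4,000 trials), adding Visit 5 raised the standard error of the change contrast:

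| Correlation | SE without → with Visit 5 | Root-mean-square error without → with |
|---|---|---|
| 0.5 | 1.16 → 1.19 | 1.19 → 1.19 |
| 0.7 | 1.12 → 1.17 | 1.18 → 1.17 |
| 0.85 | 1.10 → 1.16 | 1.21 → 1.16 |

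Under purely random loss of a fraction m, the variance ratio is [(R₂ − R₁) + (1 − R₂)/(1 − m)] / [(1 − R₁)/(1 − m)]. Here R₁ = 0.27² = 0.073, and R₂ is the squared multiple correlation of Week 4 with baseline and Visit 5. At correlation 0.7 and m = 0.1, R₂ = 0.497 and the ratio is 0.954, an SE 2% smaller. Across correlations 0.5 to 0.85 the SE falls 1% to 4% at 10% loss and 2% to 7% at 20% loss. With nothing missing there is no gain.

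**The case against.** A reader might infer that the follow-up effects are biased and less precise than the data allow. The documents do not support that.

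- **Imputation.** Multiple imputation is planned and carries over to follow-up. If Visit 5 enters it, two-visit analysis models are sound. The article does not list the imputation variables, but these commonly belong in the statistical analysis plan, so that silence is not an error. This stands, and it makes the bias conditional.
- **Discontinuation.** The text says patients are discontinued, not that ratings stop. If they are still rated, the rule creates no missing data. This also stands.
- **Well patients staying away.** A reader might infer that responders have less reason to attend Week 4, since the open-label offer goes to non-responders. That offer depends on the Week-4 score, not on Visit 5, and the documents say nothing about who stays away. If 30% of Visit-5 responders and 5% of others are assumed to skip Week 4, the estimate is still 2.86 to 2.92.
- **Precision.** Under the discontinuation rule, adding Visit 5 raises the standard error slightly. The precision claim falls.
- **Stakes.** The analyses are secondary, the shortfall in the main scenario is under half a standard error, and its direction is against the active arm, so it cannot create a false claim of durability.
- **A longer model.** The section adds that the mixed model will estimate the effect over the whole treatment course. It defines no such model, and treatment ends at Visit 5, so this does not bring Visit 5 into the follow-up fits.

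What remains is a stated analysis choice, the two-level time factor repeated at each visit, for which a better method is available from data already scheduled.

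**Conclusion.** The point holds in conditional form. The stated follow-up models omit the Visit-5 HRSD-17 although discontinuation depends on it. If discontinued patients are not rated afterwards and the imputation leaves out Visit 5, a true 3.0-point Week-4 effect is estimated at about 2.5 to 2.8, and lower under more extreme loss. Using Visit 5 brings it back to about 3.0.

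The size rests on baseline means and SD, sham improvement and between-visit correlations that the documents do not give. Only SD 8, correlation 0.27 and the 3-point difference are the protocol's. The primary Visit-5 contrast is untouched. With complete data, or with no true effect at any visit, the approaches agree. The gain is protection against bias, with overall error about equal or slightly smaller. It is not a smaller standard error. The change is worth making because it is simple and protects the only randomised evidence on persistence.

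**What to change.** Replace the three two-visit fits by one mixed model for HRSD-17 with time at four levels (baseline, Visit 5, Week 1, Week 4), group, group-by-time and an unstructured covariance. Keep the Visit-5 group contrast as primary and read the Week-1 and Week-4 contrasts from the same fit. Use the same approach for HRSD-6, SSI, BDI-II and GAD-7. If multiple imputation is kept, include all visits in the imputation model. State whether discontinued patients are still rated at Weeks 1 and 4, so that the reader can tell whether the rule creates missing data.

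The cost is wording, slightly more analysis work and possibly a slightly larger standard error at follow-up. No new data are needed, and nothing is lost if the data are complete.

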An independent, blinded rater at each site will administer the clinical assessment scales the week before and after the final treatment and at four weeks post-treatment. At baseline, participants will be asked about their expectancy of improving following the treatment course using the Stanford Expectancy Scale [41]. In addition, to assess the integrity of blinding, after their first treatment day and at the 4-week follow-up (for participants)/1-week follow-up (for technicians), all patients and technicians will be asked whether or not they believe the active or sham treatment was delivered along with their degree of certainty (0 guess – 10 certain). Collecting this information will help determine the extent of underlying placebo or nocebo effects concerning their expectations and therapeutic outcomes [42, 43].

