#### Clinical assessments during and after treatment

Clinical measures will be assessed the week before treatment and immediately after treatment completion (Friday, Visit 5), as well as at 1 and 4 weeks after treatment completion. The schedule of assessments is located in Table 1.

To compare results to other depression studies, we will examine depressive symptoms using clinician-rated and self-report scales. Secondary outcome measures will include the HRSD-6, SSI, the self-rated BDI-II, and the GAD-7. Female participants will also complete a complete reproductive history the week before treatment since the effects of high-frequency rTMS have been shown to vary based on circulating hormones [60].

**Table 1 Tab1:** Schedule of Assessments

Clinical Assessment Scales*	Screening and Baseline	Treatment Course 1		Follow-up Period 1			Treatment Course 2		Follow-up Period 2	
	Week 0	Visit 1,2, 3,4	Visit 5	Week 1	Week 4		Visit 1,2, 3,4	Visit 5	Week 1	Week 4
MINI	X									
TASS	X									
GAD-7	X		X	X	X			X	X	X
PHQ-9	X									
SSI	X		X	X	X			X	X	X
HRSD-17	X		X	X	X			X	X	X
HRSD-6	X		X	X	X			X	X	X
ATHF	X									
BDI-II	X	X	X	X	X		X	X		X
Side effect report	X	X	X	X	X		X	X	X	X
Reproductive history (females only)	X						X (prior to Visit 1 only)			
Substance Use Questions	X	X	X				X	X		
Stanford Expectancy Questionnaire	X						X (prior to Visit 1 only)			
HCS				X					X	
Group Assignment (participants and technicians)		X (after visit 1)		X	X					

MINI: Mini-International Neuropsychiatric Interview; TASS: Transcranial Magnetic Stimulation Adult Safety Screen; GAD-7: Generalized Anxiety Disorder 7-Item; PHQ-9: Patient Health Questionnaire 9-Item; SSI: Scale for Suicidal Ideation; HRSD-17: 17 Item Hamilton Rating Scale for Depression; HRSD-6: 6 Item Hamilton Rating Scale for Depression; ATHF: Antidepressant Treatment History Form; BDI-II: Beck Depression Inventory; HCS: Human Connections Scale

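### The alliance scale (HCS) is planned as a modifier of the day-5 HRSD-17 effect but is collected about a week after that outcome, so the exploratory analysis cannot show that alliance influenced it

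*Protocol article*

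**What the plan says.** Three places in the Protocol article bear on this.

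- **Analysis.** Exploratory Outcome Analyses plans a multivariable regression on whether treatment resistance, expectancy, "patient experience, or HCS modify the baseline adjusted treatment effect on the HRSD-17 (at day 5"). A second regression, for the open-label course, is to "explore how prior treatment condition, expectancy, and HCS score impact the baseline adjusted treatment effect in the open-label 1 Hz" group.
- **Purpose.** The text after Fig. 1 says that "a modified Human Connections Scale (HCS) will be administered following each treatment course (blinded and open label"), and that the aim is "to determine the impact of the patient’s sense of alliance with the technician on the therapeutic outcome". The purpose is directional: alliance acts on outcome.
- **Timing.** Under Clinical assessments during and after treatment, the clinical measures are taken in the week before treatment and then "immediately after treatment completion (Friday, Visit 5), as well as at 1 and 4 weeks after treatment completion". In Table 1 the HCS row has two marks, at Week 1 of Follow-up Period 1 and Week 1 of Follow-up Period 2.

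Of the other proposed modifiers, treatment resistance is a randomisation stratum. For expectancy, Randomization and blinding states: "At baseline, participants will be asked about their expectancy of improving following the treatment course using the Stanford Expectancy Scale".

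**The concern.** An effect modifier should be fixed before the treatment can act on it, and certainly before the outcome is observed. HCS meets neither condition for the day-5 outcome. By Week 1 a patient has finished the course and knows how they feel. If improvement makes a patient think better of the technician, HCS is partly a consequence of the day-5 score, and the regression cannot tell this from alliance producing the improvement.

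At stake is the interpretation of the non-specific component of treatment. The Discussion names the patient-technician relationship among the features through which the trial may shed light on non-specific effects. A reverse-caused association could be published as an alliance effect.

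**Working it through.** **1. Order of measurements (Table 1, first course).**

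| | Week 0 | Visits 1-4 | Visit 5 | Week 1 | Week 4 |
|---|---|---|---|---|---|
| HRSD-17 | X | | X | X | X |
| HCS | | | | X | |

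The second course repeats this pattern from its Visit 5 onward. The text on HCS timing agrees with the table: the scale comes after the course. No planned HCS rating precedes the Visit 5 HRSD-17.

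**2. Analysis size.** The Sample size section gives 105 per group for a 3-point difference, SD 8, correlation 0.27 and 80% power. With a baseline-adjusted SD and two-sided alpha 0.05 (assumed, as that section does not state alpha): 2 × (1.96 + 0.84)² × 8² × (1 − 0.27²) / 3² gives 104, within one patient of the plan. I use 2 × 105 = 210. The point changes no sample-size figure.

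**3. Main-effects model under pure reverse causation.** Let Y be the baseline-adjusted day-5 outcome, T the arm and H the HCS score. Suppose alliance has no effect:

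Y = τT + e, H = bY + u, with within-arm correlation ρ between Y and H.

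Regressing Y on T and H, the coefficient of H is ρ²/b. The coefficient of T is τ − (ρ²/b)(bτ) = τ(1 − ρ²). The test of H has t = ρ√(207/(1 − ρ²)), with 210 − 3 = 207 degrees of freedom. The documents give no ρ, so a range is assumed.

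| ρ | Shrinkage ρ² | A true 3 points becomes | t for HCS |
|---|---|---|---|
| 0.3 | 9% | 3 × 0.91 = 2.73 | 0.3 × √(207/0.91) = 4.5 |
| 0.5 | 25% | 3 × 0.75 = 2.25 | 0.5 × √(207/0.75) = 8.3 |

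**4. The modifier test itself.** A modifier question is an HCS-by-group interaction. Within an arm with outcome variance s², the slope of Y on H is b·s²/(b²s² + var(u)). If s² is equal in both arms the slopes are equal and no false interaction arises; if s² differs, the slopes differ.

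A simulation shows the size: 105 per arm, true effect −3, correlation 0.27, 2,000 runs per setting, with HCS driven only by improvement. The baseline SD of 5, the arm SDs other than 8, and ρ are assumptions.

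| ρ | Arm SDs | HCS main effect significant | Interaction significant | Effect adjusted for HCS |
|---|---|---|---|---|
| 0 | 8, 8 | 5% | 4.5% | −2.96 |
| 0.2 | 8, 8 | 77% | 5% | −2.89 |
| 0.2 | 8, 6 | 74% | 10% | −2.89 |
| 0.2 | 9, 5 | 76% | 24% | −2.89 |
| 0.3 | 8, 8 | 99% | 4% | −2.79 |
| 0.3 | 8, 6 | 97% | 16% | −2.75 |
| 0.3 | 9, 5 | 98% | 45% | −2.74 |
| 0.5 | 8, 8 | 100% | 5% | −2.33 |
| 0.5 | 8, 6 | 100% | 32% | −2.36 |
| 0.5 | 9, 5 | 100% | 83% | −2.36 |

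The shrinkage is slightly less than in step 3 because ρ here is the overall correlation with change from baseline. The within-arm, baseline-adjusted correlation is a little lower.

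**The case against.** The strongest reply is that the figures in step 3 come from a model without an interaction term, whereas the article asks about modification. That stands: with equal outcome spread the interaction test keeps a false-positive rate near 5%, and the article gives only one SD, 8. A reader might infer that the planned modifier test would routinely give false positives; the documents do not support that.

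Three further limits also stand.

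- **Efficacy.** A reader might infer that the trial's efficacy estimate is biased. It is not. The primary mixed model contains group, time and their interaction, without HCS, and nothing offers the HCS-adjusted coefficient as the efficacy result.
- **Open-label course.** A reader might infer that this regression has the identical fault. Its outcome time is not given, and the preceding sentence lists 5 days, 1 week and 4 weeks. With a Week-4 outcome, HCS would come first. There is also no concurrent randomised arm, so the shrinkage formula does not carry over directly.
- **Usefulness of HCS.** A reader might infer that the scale is worthless as collected. A by-arm comparison and a described association remain available. Alliance can be rated only after contact, so a post-course rating has a rationale.

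The exploratory label does not dispose of the point. The stated aim is still the effect of the patient's "sense of alliance with the technician on the therapeutic outcome", and no later analysis wording can place a Week-1 rating before day 5.

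**Conclusion.** The point holds for the modifier or causal reading, which is the reading the article states. HCS is measured after randomisation and about a week after the day-5 outcome, so improvement can drive it, and the planned regression cannot show that alliance affected that outcome.

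The size depends on an assumed correlation and on HCS being purely a consequence of improvement. With ρ from 0.3 to 0.5, a main-effects model would show a false HCS association (t from 4.5 to 8.3) and a treatment coefficient 9% to 25% too small. The interaction test is distorted mainly if outcome spread differs between arms. The open-label regression is affected if its outcome is day 5 or Week 1. The primary analysis and sample size are unaffected, so this is worth correcting but does not threaten the main conclusion.

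**What to change.** 1. Remove HCS from the day-5 modifier model. Keep as modifiers only variables measured before treatment: treatment resistance and baseline expectancy. (I say before treatment because the article does not fix whether expectancy is asked before or after randomisation.)
2. Report HCS by arm as a post-randomisation process measure.
3. In both courses, relate Week-1 HCS to Week-4 HRSD-17, adjusted for baseline, Visit 5 and Week 1 HRSD-17. The Week 1 adjustment matters because improvement between Visit 5 and Week 1 could also raise HCS. State the outcome time of the open-label regression.
4. Describe any relation between HCS and the day-5 score as an association only.

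The cost is a change of wording, since Table 1 already collects every measure needed. The downside is that the Week-4 analysis addresses only later change and loses patients without Week-4 data. It also remains observational, although the time order is right.

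Moving HCS to a visit before the Visit 5 rating is less attractive. Recruitment began in February 2020, so the change would split the HCS data by timing. An earlier rating would also still be post-randomisation and open to early improvement.
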